**3.7 Estimation of STI co-infection**

To broadly evaluate the prevalence and incidence of STI co-infection for the STIs/BV under consideration, the percentage of participants co-infected with two STIs/BV will be estimated. STI co-infection estimates will be estimated by population type (based on overall study population enrolled) defined as higher-risk or clinic/community-based populations and within population type by age group. For co-infection estimates, the denominators will be limited to those participants who were tested for the two STIs under consideration. See Supplemental Table 3. If resources allow, additional co-infection analyses will estimate the number of STIs/BV diagnoses received by participants (e.g., 0, 1, 1-2, 3+).

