**2. OBJECTIVES**

Using individual level data from the 18 prospective, longitudinal studies included in the HC-HIV meta-analysis dataset, we will estimate the prevalence and incidence of selected STIs/BV among women in sub-Saharan Africa and investigate potential differences by region, population type, and demographic characteristics.

Specifically, we will investigate the following objectives:

1. To evaluate the prevalence of selected STIs (chlamydia, gonorrhea, trichomoniasis, syphilis, and HSV-2) and BV among women in sub-Saharan Africa by region, population type, time period, age, and pregnancy status.
   1. To evaluate the prevalence of co-infections among the STIs/BV
2. To evaluate the incidence of selected STIs (chlamydia, gonorrhea, syphilis, trichomoniasis,and HSV-2) among women in sub-Saharan Africa by region, population type, time period, and age.
   1. To evaluate the incidence of co-infections among the STIs

The term “STIs/BV” may refer to up to 6 conditions: gonorrhea, chlamydia, syphilis, trichomoniasis, HSV-2, and/or BV. For each objective, the precise conditions included were determined by the biological/ epidemiological basis for the particular research question, the availability of STI/BV-specific data at different time points, the validity of combining test results across studies or of calculating incidence for a given condition, and other methodological and biological considerations. See Section 3.3 for more details. Human papillomavirus (HPV) is not included as the majority of studies did not include HPV data.

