**3.4. Definition of prevalence and incidence**

Prevalent STI/BV infections will be defined by diagnosis at the baseline visit. Infections will be coded as positive, negative, or missing/not classifiable/not collected or asked. Positive syphilis cases will be further categorized based on rapid plasma regain (RPR) titer testing as high titer active infection, low titer infection or unknown RPR titer infection.

Infections defined as:

Chlamydia: Positive: Positive nucleic acid amplification test (NAAT), enzyme immunoassay (EIA), or hybrid capture test

Gonorrhea: Positive: Positive NAAT, or culture

Trichomoniasis: Positive: Positive NAAT, InPouch culture, or wet mount

HSV-2: Positive: Positive type-specific serologic test

BV: Positive: Nugent score (≥7), Ison-Hay grade (≥Grade III), or Amsel criteria (≥ 3 criteria)

Syphilis (see Appendix table 4):

Positive (overall): positive RPR AND positive treponemal test (*Treponema pallidum* hemagglutination assay [TPHA], *Treponema pallidum* particle agglutination assay [TPPA] or Determine TP rapid test)

With subclassification based on RPR titer testing:

Positive, high titer active infection: positive RPR with a titer ≥1:8 AND positive treponemal test

Positive, low titer infection: 1) positive RPR with a titer <1:8 AND positive treponemal test

Positive, unknown RPR titer infection: 1) positive RPR with missing titer AND positive treponemal test

Negative: 1) negative RPR or 2) positive or missing RPR AND negative treponemal test

Missing: 1) positive RPR AND missing treponemal test or 2) missing RPR AND missing or positive treponemal test

For estimation of incident infections, individual study protocols will be reviewed to assess time frames of repeat STI testing, types of laboratory tests used, treatment information for curable STIs. For chlamydia, gonorrhea, trichomoniasis, and HSV-2, incident infection will be defined as the first positive laboratory test following a previously negative result for the infection. For trichomoniasis, incidence estimations will be limited to those studies where *T. vaginalis* testing was done using InPouch or NAAT. For syphilis incidence, using the categories defined above, an incident infection will be defined as:

1. participants who are negative at baseline who are diagnosed at a follow-up visit with a positive infection OR

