| #1 ([name]) | | Yes | | About 70% tested on every FU visit | EIA | Yes | Every FU visit | Culture | Yes | Yes including prevalent and incident HSV2 result | Focus EIA | | Yes | | Yes | Wet mount | Yes | | Some Fup visits | RPR/ TPHA | Yes | Nugent |
| #2 ([name]) | | Yes | | No | Hybrid capture GC/CT DNA assay | Yes | No | Hybrid capture GC/CT DNA assay | No | No | N/A | | Yes | | Some  FU visits | Wet mount | No | | No | N/A | Yes (subset) | Amsel and Nugent |
| #3a/b ([name]) | | Yes | | Every FU visit | NAAT | Yes | Every FU visit | NAAT | Yes | Yes including prevalent and incident HSV2 result | Focus  EIA | | Yes | | Yes | Wet mount | Yes | | Every 6 months | RPR/ TPPA/  TPHA | Yes | Amsel and Nugent |
| #4  ([name]) | | Yes | | >50% tested on FU2 (6M) Fewer tested on other FU visits | PCR | Yes | >50% tested on FU2 (6Mt)  Fewer tested on other FU visits | Culture/  PCR | Yes | Yes, only prevalent HSV2 result | ?? | | Yes | |  | ?? | Yes | |  | RPR/ TPPA/TPHA | Yes | Nugent |
| #5 ([name]) | | Yes | | At 6 and 12 months | PCR | Yes | At 6 and 12 months | PCR | Yes | At baseline and Final visit | IgG Kalon | Yes | | | No | N/A | Yes | | Some  FU visits | RPR/ TPPA | Yes | Nugent |
| #6 ([name]) | | Yes | | At 6, 12, 24 and 30 months | PCR | Yes | At 6, 12, 24 and 30 months | PCR | Yes | Yes  Had to be HSV-2 positive at baseline to join trial | IgG Kalon | Yes | | | At baseline, 6, 12, 24 and 30 months | In pouch and wet mount | Yes | | At baseline, 6, 12, 18, 24 and 30 months | RPR/ TPPA/ | Yes | Nugentand Ison Hay at baseline; Ison Hay at Fup |
| #7a/b ([name], [name]) | | Yes | | Every FU visit | PCR | Yes | Every FU visit | PCR | Yes | Yes including prevalent & incident HSV2 result | FocusELISA | Yes | | | Yes | PCR | Yes | | Final visit only | RPR/ TPHA | Yes, if symptomatic | Amsel |
| #8 ([name], [name]) | | Yes | | Every FU visit |  | Yes | Every FU visit | ?? | All ulcer+, random- | All ulcer+, random- | N/A | Yes | | |  | ?? | Yes | |  | TPPA/TPHA | Yes | Nugent |
| #9 ([name]) | | Yes | | >90% tested on FU2 (6M) & 4 (12M) Few tested on the other visits (max FU4) | ?? | Yes | >90% tested on FU2 (6M) & 4 (12M) Few tested on other visits (max FU4) | ?? | Yes | Yes including prevalent and incident HSV2 result |  | Yes | | |  | ?? | No Lab Form | |  | No Lab Form |  | Yes |

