**Table 5. Planned tables and forest plots**

| **Analysis objective** |  | **Meta-analysis output/presentation** | | | |
| --- | --- | --- | --- | --- | --- |
|  | **Analysis population** | **Baseline table** | **Heterogeneity evaluation** | | **One-stage stratified analysis and two-stage random effect analysis** |
|  |  |  | **I^2^** | **Forest plot** |  |
| **Primary** |  |  |  |  |  |
| **To evaluate the prevalence of selected STIs/BV: gonorrhea, chlamydia, syphilis, trichomoniasis, HSV-2, and/or BV** | **All studies** | **√** | **√** | **√** | **√** |
|  | **Region**: South Africa, Eastern Africa, Southern Africa | **√** | **√** |  | **√** |
|  | **Population type**: higher-risk or clinic/community-based populations | **√** | **√** |  | **√** |
|  | **Time period**: baseline data were collected prior to 2002, during 2003 to 2006 2007 or later | **√** | **√** |  | **√** |
|  | **Age**: 15-49 years, 15-24 years, 25-49 years | **√** | **√** | **√** | **√** |
|  | **Pregnancy**: pregnancy status at baseline | **√** | **√** |  | **√** |
|  | **Cross-stratum (Region, Population type, Time period, Age, Pregnancy)**^1^ | **√** | **√** |  | **√** |
| **To evaluate the incidence of selected STIs: chlamydia, gonorrhea, and HSV-2** | **All studies** | **√** | **√** | **√** | **√** |
|  | **Region**: South Africa, Eastern Africa, Southern Africa | **√** | **√** |  | **√** |
|  | **Population type**: higher-risk or clinic/community-based populations | **√** | **√** |  | **√** |
|  | **Time period**: baseline data were collected prior to 2002, during 2003 to 2006 2007 or later | **√** | **√** |  | **√** |
|  | **Age**: 15-49 years, 15-24 years, 25-49 years | **√** | **√** | **√** | **√** |
|  | **Pregnancy**: pregnancy status at baseline | **√** | **√** |  | **√** |
|  | **Cross-stratum (Region, Population type, Time period, Age, Pregnancy)**^1^ | **√** | **√** |  | **√** |
| **Secondary** |  |  |  |  |  |
| **To evaluate the prevalence of co-infections of selected STIs/BV: gonorrhea, chlamydia, syphilis, trichomoniasis, HSV-2, and/or BV** | **All studies** |  | **√** |  | **√** |
| **To evaluate the incidence of co-infections among the STIs: chlamydia, gonorrhea, and HSV-2** | **All studies** |  | **√** |  | **√** |
| **Sensitivity Analysis** |  |  |  |  |  |
| **To evaluate the prevalence of gonorrhea, chlamydia, syphilis, and BV based on the type of diagnostic criteria** | **All studies** |  | **√** |  | **√** |

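### Incident co-infection is given the same measure as prevalent co-infection, a percentage of women tested for both infections, so it varies with follow-up length and, for pairs with HSV-2, with baseline HSV-2 prevalence

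*Protocol*

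**What the plan says.** Incident co-infection is a named aim under objective 2 in section 2: "To evaluate the incidence of co-infections among the STIs". The study summary lists co-infection as a secondary objective.

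Section 3.7 gives one measure for prevalent and incident co-infection alike: "evaluate the prevalence and incidence of STI co-infection for the STIs/BV under consideration, the percentage of participants co-infected with two STIs/BV will be estimated". It adds one rule on the denominator: "For co-infection estimates, the denominators will be limited to those participants who were tested for the two STIs under consideration". It does not say whether the two infections must be present at the same visit, whether both must be new, or over what period they are counted.

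Single infections are treated differently. In section 3.4, for chlamydia, gonorrhea, trichomoniasis and HSV-2, "incident infection will be defined as the first positive laboratory test following a previously negative result for the infection". Section 3.5 sets a censoring rule, and section 5.2.1 names Poisson regression for each selected STI. All three are written infection by infection, and none is extended to pairs.

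Table 5 lists the secondary analysis as "To evaluate the incidence of co-infections among the STIs: chlamydia, gonorrhea, and HSV-2", over all studies, with an I² and both one-stage and two-stage analysis.

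**The concern.** A percentage among women tested for both infections is a sound measure at one visit. Over follow-up it rises with time under observation, and the studies were not tested for equally long. Two studies with the same underlying rate would report different percentages. Pooling them would give a figure tied to no time period, and the I² would partly reflect study duration. Comparisons by population type and age group, which section 3.7 plans, would carry the same distortion wherever follow-up differs between the groups.

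HSV-2 adds a second difficulty. A woman who is HSV-2 positive at baseline cannot have an incident HSV-2 infection under section 3.4, yet section 3.7 keeps her in the denominator. Whether her established infection may form half of an incident co-infection is not stated. The exclusion in section 3.2 of studies that required the diagnosis for entry works at study level. It does not remove HSV-2 positive women from the other studies.

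The length-of-follow-up sensitivity analysis in section 5.3 would not show the problem, because its suggested split is at 3 months.

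**Working it through.** The protocol states no co-infection rate or percentage, so there is no figure of its own to reproduce. All rates and prevalences below are assumptions. The testing schedules come from Appendix Table 3, which is marked as still to be updated.

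**1. Follow-up length**

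Inputs: chlamydia and gonorrhea testing to 12 months in studies 5, 9 and 14 and to 24 months in study 12; a constant joint rate λ of first co-infection.

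- Percentage by time T (years) = 1 − exp(−λT).
- λ = 0.03: T = 1 gives 1 − exp(−0.03) = 2.96%; T = 2 gives 1 − exp(−0.06) = 5.82%.
- The ratio of 24 to 12 months is 1 + exp(−λ) = 1.97.

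| Joint rate per 100 woman-years | 12 months | 24 months | Ratio |
|---|---|---|---|
| 1 | 1.00% | 1.98% | 1.99 |
| 3 | 2.96% | 5.82% | 1.97 |
| 5 | 4.88% | 9.52% | 1.95 |
| 10 | 9.52% | 18.13% | 1.90 |

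A rate does not behave this way. Expected person-time per woman up to first co-infection is (1 − exp(−λT))/λ. With λ = 0.03 this is 0.985 years at 12 months and 1.941 years at 24 months. Events over person-time are 0.02955/0.985 and 0.05824/1.941, both 3 per 100 woman-years.

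Appendix Table 3 shows no HSV-2 data for study 12, so this particular contrast concerns the chlamydia/gonorrhea pair.

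**2. Baseline HSV-2 prevalence (chlamydia/HSV-2 pair)**

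Inputs, all assumed: 10 per 100 woman-years for each infection, independent, T = 1 year, baseline HSV-2 prevalence p. Each cumulative risk is c = h = 1 − exp(−0.1) = 9.52%. For simplicity the illustration counts both infections at any time in the year.

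- At-risk women only, both new: c·h = 0.91%.
- All women tested, both must be new: (1 − p)·c·h.
- All women tested, prevalent HSV-2 counts: c·[p + (1 − p)·h].

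| p | Both must be new | Prevalent HSV-2 counts |
|---|---|---|
| 20% | 0.72% | 2.63% |
| 50% | 0.45% | 5.21% |
| 80% | 0.18% | 7.79% |

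With 15 (chlamydia) and 5 (HSV-2) per 100 woman-years the pattern is the same. The at-risk value is 0.68%, and for p from 20% to 80% the two readings run from 0.54% down to 0.14% and from 3.33% up to 11.28%.

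Either way the result depends on p, in opposite directions. Table 5's three infections form three pairs, two of which contain HSV-2. Chlamydia/gonorrhea does not involve p.

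**The case against.** Several points on the other side carry weight.

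- A percentage newly infected can be a cumulative incidence. A reader might infer that section 3.7 measures follow-up length and HSV-2 prevalence instead of incidence, and that goes too far. The fault is narrower: the percentage is tied to neither a fixed horizon nor an at-risk group.
- A reader might take the contrast as 12 against 30 months, since study 6 tested for chlamydia and gonorrhea "At 6, 12, 24 and 30 months". But its gap from 12 to 24 months appears to fail the six-monthly testing rule in section 3.2, and it required HSV-2 positivity at entry, which excludes it from HSV-2 incidence. On the criteria as written it enters none of the three pairs.
- A roughly 5-fold effect can be produced by multiplying two separate cumulative risks up to 30 months. That counts women who ever had both infections, perhaps many months apart. Section 3.7 speaks of women being co-infected, which most naturally means at the same time.
- A reader might also infer that prevalent HSV-2 simply lowers the figure, halving it at 50% prevalence. That holds only if both infections must be new, and the opposite reading is equally open.
- Table 5 sends co-infection to the one-stage and two-stage analyses, where incidence means Poisson regression. But section 5.2.1 words that model for single STIs, and section 3.7 states another measure for pairs.
- Supplemental Table 3 is cited but not at hand. Its title concerns stratifications, which gives no sign that it changes the measure, though this cannot be checked.

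The objections limit the size and the wording of the point. The stated measure and its denominator remain as they are.

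**Conclusion.** The point holds in a limited form. Section 3.7 fixes a measure for incident co-infection that departs from the protocol's own incidence method and is not comparable between studies followed for different lengths of time. This is a stated rule, not a detail left for a later document. The follow-up effect is about 2-fold between 12 and 24 months (1.90 to 1.99 over assumed joint rates of 10 down to 1 per 100 woman-years), provided the rate is constant and follow-up is complete to those visits.

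For the two HSV-2 pairs, dependence on baseline prevalence is certain under either reading. Its direction cannot be determined from the protocol, and its size rests on assumed rates. The chlamydia/gonorrhea pair is affected by follow-up length only. Prevalent co-infection and the primary prevalence and incidence estimates are untouched. The change is worth making before analysis, but it concerns a secondary objective only.

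**What to change.** In section 3.7, and in the incident co-infection row of Table 5:

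1. Keep the percentage among women tested for both infections for baseline (prevalent) co-infection only.
2. Define an incident co-infection as both infections present at the same visit in a woman previously without that co-infection.
3. Treat HSV-2 as persisting once positive, and date seroconversion by the midpoint rule of section 3.4. This is needed because HSV-2 was not always tested when the curable STIs were: study 5 tested it only at baseline and the final visit, but chlamydia and gonorrhea at 6 and 12 months. Say how a visit that falls exactly on the midpoint is classed.
4. Count person-time from the first visit at which she is negative for at least one of the pair, up to the first co-infection or the last visit with testing.
5. Report a rate per 100 woman-years with the Poisson model of section 5.2.1.
6. Report HSV-2 pairs separately by baseline HSV-2 status, so that a new curable STI on established HSV-2 is not mixed with two new infections.

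The work uses data already held. The cost is fewer events per pair, wider intervals and some extra programming, mainly for HSV-2 status at visits without an HSV-2 test.

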**3.8. Assessment of the risk of bias in individual studies**

All studies included in the HC-HIV meta-analysis dataset are cohort studies or randomized trials.

Knowledge of methodological features that can bias study results is important for interpreting the findings from individual studies and how the differences between studies might contribute to heterogeneity in study results. Unlike meta-analyses based on aggregated data, which generally rely only on information within published papers, an in-depth assessment of the risk of bias in individual studies will be possible. The assessment will make use of the individual participant data, study protocols, clinical study reports, available publications and communications with the study investigators. Additional factors can be assessed, such as whether those lost to follow-up were systematically different to those who remained in the study.

This process has already been completed for the HC-HIV IPD meta-analysis but will be revisited to include issues related to the assessment of STI prevalence and incidence. Using the study protocol, published articles and data sent by the studies, two reviewers will assess independently the following items (no score will be used) that has been adapted from the Strengthening the Reporting of Observational Studies (STROBE) statement and checklist:

For objectives 1 and 2:

1. How much data on STIs/BV are missing?
2. Were important covariates measured in the study?
3. Were appropriate STI/BV diagnostic tests used?

For objective 2:

1. Was the level of retention high in the study (>80% at 12 months)?
2. How frequently were STIs measured?

**4. DATA MANAGEMENT**

The HC-HIV meta-analysis dataset will be used as the base for this STI meta-analysis. This dataset was established in accordance with ethics guidelines, and the Protection of Human Subjects Committee of FHI 360 approved the study and judged it as exempt research (PHSC #10263). All included studies had relevant country-specific institutional ethical review and regulatory board approvals, and all participants within each study provided written informed consent for study participation. No information that could identify an individual woman was obtained in establishing the HC-HIV dataset. A unique number was assigned to each study and each woman. A list with the HC-HIV IPD meta-analysis identification numbers and the study identification numbers from the original 18 studies was retained in case clarification about specific variables was needed.

To create the final analytic dataset for the STI analysis, any additional variables needed will be requested through a data format sheet. The data format sheet includes the instructions for numerical coding, with the question number to which each variable relates and the required format. The study/data manager from any of the original 18 studies from which data are needed will send the data format sheet and the corresponding data to a designated biostatistician at FHI360. Variables from each study will be recorded if necessary, using pre-specified categories. The categories will depend on the consistency of coding between studies. Once the final analytic dataset for the STI analysis is completed, the link between the STI meta-analysis identification numbers and the HC-HIV dataset numbers will be destroyed. All the data will be stored securely on the access required storage drive.

**5. ANALYSIS**

The following sections and Table 1 describe the statistical methods that will be used to investigate the objectives and hypotheses in Section 2. We will use descriptive statistics and statistical tests to examine between-study heterogeneity and univariable and multivariable methods for the analysis of IPD. Table 5 provides a summary of the planned forest plots and tables.

**5.1 Descriptive Analysis**

We will conduct descriptive analyses before proceeding to meta-analyses in order to gain a detailed understanding of the data received within and between studies. Descriptive statistics will be used to summarize study participant characteristics (i.e. socio-demographic characteristics, risk behaviors, and study duration, etc.) by each study and overall.

Categorical variables or continuous variables that have been categorized will be summarized by frequencies and percentages and analyzed using Cochran-Mantel-Haenszel tests across study groups and sites. Data recorded for continuous variables will be summarized by medians and ranges and analyzed by Wilcoxon Mann Whitney tests among the study groups and/or sites.

**5.2. Meta-analysis**

We will conduct meta-analysis of individual participant data using both one- and two-stage meta-analysis approaches [25]. Each method has advantages and disadvantages. When both methods are used, they can provide valuable complementary information.

**5.2.1 Two-stage meta-analysis**

We will use two-stage meta-analysis as our primary approach to examine prevalence and incidence estimates. Using this method, participants in each study are compared directly only with other participants in the same study. The two-stage method is well suited to assess between study heterogeneity. While the method is less suitable for identifying prognostic factors (due to the different sets of covariates measured across datasets), it is possible to assess effect modification.

In the first stage, IPD in each study are analyzed separately to obtain summary statistics. We will use binomial regression models to estimate prevalence estimates for each selected STI/BV and Poisson regression to estimate the incidence for each selected STI.

If appropriate, the second stage is to use standard meta-analysis techniques to combine the summary measures to give an overall estimate of prevalence and incidence across studies by population-type. The decision to combine results and conduct further analyses using random and/or fixed effect models depends on the level of between-study heterogeneity.

The same approach will be used to estimate prevalence and incidence for each stratum of interest based on region, population type, age, pregnancy status, and time period of the study.

